## Abstract

The aim of the study is to investigate the relationship between physical activity as assessed by accelerometers and cognitive development across the human age ranges (from children and adolescents to adults). Additionally, this study seeks to explore whether physical activity contributes to cognitive development via modification of plasma insulin-like growth factor 1 (IGF-1) and brain-derived neurotrophic factor (BDNF). In the study, 500 preschool children (3.5–5.5 years old) are taking part in 6 triennial assessment waves over the span of 15 years. At each wave, participant measures included (a) 7-day physical activity monitoring using ActiGraph's GT3X accelerometers, (b) the evaluation of cognitive development, (c) anthropometric and physical fitness assessments, (d) plasma IGF-1 and BDNF concentrations, and (e) retrospective questionnaires. Linear regression models are used to examine the effect of physical activity on cognitive development; plasma IGF-1 and BDNF concentrations are considered as mediators into data analyses. The results of the study may help to inform future health interventions that utilize physical activity as a means to improve cognitive development in children, adolescents, and adults. Additionally, the study may assist in determining whether the putative effects occur via modification of plasma IGF-1 or BDNF concentrations.

## 1. Introduction

The cognitive development that occurs during childhood and adolescence is essential to a person's health. Several longitudinal studies have reported that cognitive scores assessed in early life were associated with academic achievement [1], mental ability [2], and mortality and morbidity risk in later life [3–6]. Physical activity is a theoretically relevant factor that may improve cognitive function from childhood to adulthood [7–9]. The evidence that has been accumulated over the past two decades has shown that higher levels of physical activity behavior in children and adolescents are related to increases in cognitive function and academic performance, while more sedentary behavior has been shown to exert the opposite effect [7–9]. However, stronger evidence from longitudinal studies is still warranted. With that being said, it is unclear whether the associations between physical activity and cognitive development are isolated to specific ages, whether they are present throughout early life, or whether they change over time. The physical activity and cognitive development (PACD) study, a longitudinal study to investigate the relationship between physical activity and cognitive development across the human age ranges (from children and adolescents to adults), is intended to provide a holistic platform for the in-depth exploration of these issues.

It is now recognized that an accelerometer can be used as an approach to objective data collection to provide reliable and valid measurements of physical activity in children [10]. This approach has successfully been used in longitudinal studies with children as the participants [11–13]. A review found that, in 33 out of 37 studies conducted in 11 countries from America and Europe, accelerometers were used for measuring the physical activity of preschool children [14]. However, physical activity, as recorded by an accelerometer, has not been investigated in Chinese preschool children. To address this gap, the above approach is used in Chinese participants in the PACD study.

Over the past two decades, research has been conducted on insulin-like growth factor 1 (IGF-1) and brain-derived neurotrophic factor (BDNF) as to their association with cognitive function and physical activity. The accumulated evidence suggests that brain network configuration and cognitive function are regulated by IGF-1 [15, 16] and BDNF [17, 18] and that IGF-1 [19] and BDNF [20] levels are elevated by physical activity. Results from experimental animal studies demonstrate that cognitive function is positively affected by exercise, likely via IGF-1 [21] and BDNF [22]. In order to further understand and interpret the putative findings of the effect of physical activity on cognitive development in the PACD study, plasma IGF-1 and BDNF concentrations were measured as mediators in order to explore the mechanisms [22, 23].

The aim of the PACD study is to investigate the relationship between physical activity as assessed by accelerometers and cognitive development across the human age ranges (from children and adolescents to adults). Additionally, the PACD study seeks to explore whether physical activity contributes to cognitive development via modification of plasma IGF-1 or BDNF.

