### 2.6. Statistical Analyses

All of the collected data are typed into EpiData 3.1 software (EpiData Association, Odense, Denmark), double-checked by two research staff members, and exported to SPSS version 22.0 (IBM Corporation, USA) for further analyses. Descriptive statistics are used to present baseline data and the following assessment waves as mean ± SD and median (interquartile ratio, IQR) for normally distributed and nonnormally distributed data, respectively. Prior to analyses, the log and square root methods are used for nonnormally distributed data. Linear regression models are performed to examine the relation of physical activity and cognitive development over time in more detail, with LPA, MPA, VPA, MVPA, and TPA assessed by ActiGraph's GT3X accelerometers as the independent variables, Verbal IQ, Performance IQ, and Full Scale IQ as dependent variables, and data collected by retrospective questionnaires and anthropometric and physical fitness assessments as covariates or moderators [47]. Exploratory analyses are also performed in order to examine whether plasma IGF-1 and BDNF concentrations serve as the mediators for the potential positive effects of physical activity on cognitive development [48].

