## 4. Discussion

As discussed above, the accumulated evidence demonstrates that physical activity is positively associated with cognitive function and academic performance in early life [7–9]. However, stronger, more compelling evidence from longitudinal studies is still required. A systematic review of three databases of literature (SPORTDiscus, ERIC, and PubMed) from 2000 to 2013 found only three longitudinal studies done on adolescents [9]. This review reported a lack of longitudinal studies that included children's age. To address this limitation, the PACD study is designed to test whether the putative effects of physical activity on cognitive development are present from early childhood to adulthood.

In recent years, studies of the effect of physical activity on cognitive development are moving from descriptions of the relationship to in-depth explorations of the mechanisms [49–51]. The PACD study also seeks to investigate the possible role of plasma IGF-1 and BDNF in mediating activity-related cognitive development. Overall, pilot study results generally support the feasibility and acceptability of the methods and measures. However, a few modifications of the study protocol have been made to reduce participant burden and improve compliance and data quality.

At the pilot component of the study, the full C-WYCSI assessment (including 11 subsets) lasted approximately 1 h and 45 min for each child. This time frame was determined to be too arduous for the preschool children. The results of pilot study showed that Full Scale IQ scores from short form of C-WYCSI assessments were significantly correlated with those from full C-WYCSI assessments. As an alternative approach, the short form of C-WYCSI assessment lasted for 40 min for each child, which resulted in improved compliance. To reduce the stress of a lengthy assessment of the participants, the short form of C-WYCSI is used at the first assessment wave.

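### The Introduction asks whether the activity–cognition association changes with age, but the regression listed in section 2.6 has no age or wave term and so does not estimate or test that change

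*Protocol article*

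**What the plan says.** **The question.** Section 1 of the protocol article leaves open "whether the associations between physical activity and cognitive development are isolated to specific ages, whether they are present throughout early life". It names change with time as a third possibility and says that the study "is intended to provide a holistic platform for the in-depth exploration of these issues". The formal aim is broader: to "investigate the relationship between physical activity as assessed by accelerometers and cognitive development across the human age ranges". The Discussion adds that "the PACD study is designed to test whether the putative effects of physical activity on cognitive development are present from early childhood to adulthood".

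**The analysis.** Section 2.6 states: "Linear regression models are performed to examine the relation of physical activity and cognitive development over time in more detail". The predictors are five accelerometer measures, from light to total activity. The outcomes are Verbal, Performance and Full Scale IQ. Covariates or moderators come from the questionnaires and from the anthropometric and fitness assessments. Section 2.5.5 describes the questionnaire content (family, social, lifestyle, diet, well-being and similar items) and does not name age.

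**The design.** Section 2.1 gives 500 children and six waves three years apart. Section 2.5.2 gives one IQ instrument for the first wave and two others, chosen by age, for the later five.

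**The concern.** Whether an association is confined to some ages, holds throughout or changes is a question about differences between age-specific slopes. Section 2.6 does not leave the model wholly open: it itemises predictors, outcomes and moderators. The moderator that the Introduction's question needs is not among them, and although the relation is to be examined over time, no listed term carries time.

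At stake is the use made of a 15-year repeated design. A single averaged slope says nothing about age. Separate slopes without a test of difference leave any statement about age to informal comparison.

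**Working it through.** **1. Question against model**

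- A regression with only the listed terms is IQ = α + β × activity + γ × covariates + error. It has one β, averaged over whatever waves are pooled.
- The question needs IQ = α_j + β_j × activity + γ × covariates + error for waves j = 1 to 6, and a test of β_1 = … = β_6. That test has 6 − 1 = 5 degrees of freedom.
- Converting raw scores to norm-based standard scores (section 2.5.2) can remove the average age trend in IQ. It does not make β_j equal across waves, so it does not replace the interaction.

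**2. Figures in the plan**

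The article gives no alpha, power, effect size or basis for 500, so there is no power figure to reproduce. The design arithmetic agrees: (6 − 1) × 3 = 15 years, and 250 + 250 = 500.

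**3. Illustration: wave-wise fits compared by significance**

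This procedure is an inference and is not stated in the article. Inputs:

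- n = 500 (section 2.1), or about 430 if the pilot rate of valid accelerometer data carried over: 0.861 × 500 = 430.5 (section 3).
- Assumed: two-sided alpha 0.05; the same true correlation r at all six waves; r = 0.10, 0.125 or 0.15; correlation between wave estimates of 0, 0.3 or 0.6.

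Power per wave: p = Φ(atanh(r) × √(n − 3) − 1.96). Chance that some waves are significant and some are not, with independent waves: 1 − p^6 − (1 − p)^6.

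For n = 500 and r = 0.125: 0.1257 × 22.29 = 2.80; 2.80 − 1.96 = 0.84; p = 0.80. The mixed pattern then has probability 1 − 0.262 − 0.0001 = 0.738.

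The correlated columns come from 200,000 simulated studies per row.

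| n | r | Power per wave | Mixed, corr. 0 | Mixed, corr. 0.3 | Mixed, corr. 0.6 |
|---|---|---|---|---|---|
| 500 | 0.10 | 60.9% | 94.5% | 81.0% | 61.6% |
| 500 | 0.125 | 80.0% | 73.8% | 60.0% | 45.0% |
| 500 | 0.15 | 92.1% | 39.1% | 31.8% | 23.8% |
| 430 | 0.10 | 54.5% | 96.5% | 83.4% | 63.6% |
| 430 | 0.125 | 73.8% | 83.8% | 69.3% | 52.4% |
| 430 | 0.15 | 87.8% | 54.3% | 43.9% | 32.6% |

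In every cell the true association is constant. A 5-df test of equal slopes rejected in 4.9% to 5.1% of the same simulated studies, with the correlation between waves taken as known.

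**4. Instrument against age**

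Adding three years per wave to the 3.5–5.5 entry range gives nominal ages of 6.5–8.5, 9.5–11.5 and 12.5–14.5 at waves 2 to 4, all within the C-WISC range of 6–16. Wave 5 (15.5–17.5) straddles the change to WAIS-RC above 16, and wave 6 (18.5–20.5) lies wholly above it. A difference between wave 1 and wave 2, or between wave 4 and the last two, is therefore partly mixed with a change of scale.

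**The case against.** **The article is a condensed account.** Section 2.6 is one paragraph. It speaks of examining the relation over time, provides for moderators and excludes no term. A fuller analysis plan, not shown here, may contain the interaction. This limits how hard the point can be pressed, but does not remove it: the article chooses to name its moderators and omits the one that its own question calls for.

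**Is this the central question?** A reader might infer that change with age is the primary hypothesis. The documents do not support that. It is a prominent motivation in the Introduction, whereas the formal aim is the relationship across age ranges. The Discussion asks whether effects are present from childhood to adulthood; presence at each age is not the same as a difference between ages, and age-specific estimates could address it.

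**Would age claims rest on P values?** A reader might also infer that waves will be fitted separately and compared by significance. Nothing in the article says so. A pooled fit would yield no age-specific result, and wave-wise slopes could be compared through their confidence intervals. The table shows what that practice would risk, not what the plan prescribes.

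**The percentages are sensitive.** They rest on assumed effect sizes and fall markedly with correlation, which is likely when the same children are measured repeatedly. They also count any mixed pattern, even five significant waves out of six. All of this stands.

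**Conclusion.** The point holds as a mismatch between a question raised in section 1 and the model set out in section 2.6: with the terms listed, change of the association with age is neither estimated nor tested. That conclusion needs no numerical assumption.

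The 24% to 97% range is conditional on comparing significance between waves, on a constant r of 0.10 to 0.15, on 430 to 500 children at every wave and on correlations of 0 to 0.6. It does not support saying that the analysis will usually produce false age patterns: several cells lie below 50%. The point merits correction because it bears on a main reason for the repeated design. It does not put the broader aim of relating activity to cognition in doubt.

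**What to change.** In section 2.6:

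- Fit one repeated-measures model over all waves, either a mixed model with a child random effect or GEE, so that within-child correlation is handled. Include activity × wave.
- Make the joint interaction test (5 df) the analysis of whether the association changes with age.
- Report wave-specific slopes with confidence intervals from that model, and state that waves will not be compared by their significance.
- Use age-standardised IQ scores throughout, and state that a difference between waves may partly reflect the change from C-WYCSI to C-WISC to WAIS-RC. A sensitivity test confined to waves 2 to 4 (2 df), where the nominal ages fall within one instrument, would help, provided no revised version is introduced between them.
- Say which activity measure and IQ score carry the main age test, since five measures by three scores would give 5 × 3 = 15 interaction tests.

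The cost is analysis wording only. Section 3 reports that first-wave collection is still under way, so the change can precede any between-wave data. The downside is that an interaction test has less power than a main effect; a non-significant result should not be read as proof that the association is constant. The model also cannot separate age from instrument where the two change together.

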## 2. Methods

### 2.1. Research Design

The PACD study uses a long-term, longitudinal, cohort design. In the present study, 500 preschool children (3.5 to 5.5 years old) are taking part in 6 triennial assessment waves across 15 years.

### 2.2. Ethical Issues and Research Permits

The study continues to adhere to all relevant guidelines for rigorous scientific practice. Prior to enrollment, informed consents are signed by the parents or legal guardians of the participants. For participants ≥16 years of age, informed consents will also be obtained from the participants themselves. All participants in the study are volunteers. Consent can be withdrawn from the study by participants and their parents or legal guardians at any time without explanation. At each assessment wave, participants have the option to choose attending the blood sampling component or not. None of the measurements have been shown to have any significant health or safety risk in past studies. The benefits and associated risks of the study are carefully explained to the parents or legal guardians of the participants. Voluntary participation especially for blood collection is stressed.

Before the study began, two research staff members had attended a two-month training workshop to learn C-WYCSI assessment in Central South University, Changsha, China. Additionally, research staff members received training on how to engage children and obtain informed consent, complete the questionnaires, and conduct accelerometer monitoring and anthropometric and physical fitness assessments. More training workshops will also be prepared for research staff members before each assessment wave. The study doctors and nurses from hospital are available during the assessment. The present study has been approved by the Ethics Committee of Shanghai University of Sport (registration number: 2015028) and has been registered in Chinese Clinical Trial Registry (registration number: ChiCTR-OOC-15007439).

### 2.3. Participants

The participants were 500 preschool boys (*n* = 250) and girls (*n* = 250) living in urban areas of Shanghai, China. Participants were made eligible for the study after screening done via a questionnaire and a health assessment. Children were recruited from 8–10 kindergartens, based on the following inclusion criteria: (1) child is in the 2nd grade in kindergarten; (2) both child and parent/legal guardian are able to speak Mandarin; (3) informed consent is signed by the parent/legal guardian of the child. Conversely, exclusion criteria for the participants include the following: (1) health issues that limit physical activity; (2) mental illness; and (3) participation in special education programs [12]. The inclusion and exclusion criteria were assessed by two trained research staff members and doctors from the kindergartens and Xinhua Hospital affiliated to Shanghai Jiao Tong University School of Medicine. The anticipated gender breakdown is expected to be 50% male and 50% female.

Children Physical Health Research Base (CPHRB) in kindergartens was constructed before the study. Participants were recruited through a parents' information evening in the targeted kindergartens. Rewards for participants will be printed reports of the results of Intelligence Quotient (IQ) scores, physical fitness, anthropometric assessments, and so forth. If parental or legal guardian consent is given at recruitment, blood sampling is done and the printed reports for the results of blood trace element contents are provided. After the first assessment wave, both the family members of the participants who complete the assessments and the kindergarten teachers are provided with free assessment services of physical fitness.

Tracking plans are made for maintaining contact between family members of participants and the researchers, thus maximizing retention of participants. This has to be done due to the long-term period for data collection [24]. The longitudinal tracking plan includes (1) obtaining home and cell phone numbers and e-mail addresses; (2) establishing WeChat group and QQ group which have all the parents or legal guardians of participants; (3) providing all the participants and their family members with free assessment service for physical fitness annually; and (4) awarding certificates for recognizing their contribution to the longitudinal research [25].

### 2.4. Procedures

Each group of participants is on their own assessment schedule that is dependent on the time of enrollment. In order to avoid data collection during the months when the participants may have unusual patterns of physical activity, such as summer and winter months, assessments take place during the spring (March through May) and fall (September through November). The anthropometric and physical fitness assessments are performed and managed during two different time periods. They are both performed and managed either at the kindergartens during the first assessment wave or at the Exercise and Fitness Sciences Center in Shanghai University of Sport during the following 5 assessment waves.

Following the obtainment of consent, point data collection is conducted within two weeks at each assessment. Participants perform anthropometric and physical fitness assessments, evaluation of cognitive development, blood sampling, and retrospective questionnaires and receive the objective devices (accelerometers) with instructions. With the assistance of research staff members, participants and parent/legal guardians complete the questionnaires. Then participants wear the accelerometers for 7 consecutive days (including 5 weekdays and 2 weekend days) in order to monitor their physical activity behavior [26]. Participants are instructed to continue with their normal daily routines during the sessions.

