## 3. Results

The aim of this study is to describe the protocol of the PACD study. Prior to the first assessment wave, the procedures were pilot-tested for feasibility and user acceptability in a sample of 36 preschool children. At the pilot component of the study, valid accelerometer data were collected from 86.1% of children, anthropometric and physical fitness assessments were performed in 88.9% of children, venous blood samples were taken from 66.7% of children after consents were obtained for attending blood sampling, and questionnaires were completed by 94.4% of children and parent/legal guardian pairs. In addition, full C-WYCSI assessments were performed in 86.1% of children. Pearson's correlation detected that Full Scale IQ scores from short form of C-WYCSI assessments (including 4 subsets) had significantly positive correlations with those of full C-WYCSI assessments (*n* = 31; *r* = 0.90; *P* < 0.01). During the pilot study, two informed consents were withdrawn by the parents of the children. None of the accelerometers were lost, stolen, or broken. Valid data collected from the pilot study will be merged in the first assessment wave of the PACD study.

To date, 8 CPHRBs of kindergartens for the study have been established in Shanghai, China. Two more kindergartens will also be recruited into the PACD study. Participant recruitment and data collection for the first assessment wave are currently ongoing. A total of 346 children (57.5% male and 42.5% female) from the 7 kindergartens have been enrolled.

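### The regression and mediation plan states no wave pairing and does not list earlier IQ as a covariate; a same-wave model could not tell activity affecting cognition from the reverse

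*Protocol article*

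**What the plan says.** Protocol article, 2.1 Research Design: 500 preschool children are "taking part in 6 triennial assessment waves across 15 years".

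2.4 Procedures sets the order within a wave. In the first block, "Participants perform anthropometric and physical fitness assessments, evaluation of cognitive development, blood sampling, and retrospective questionnaires and receive the objective devices". After that, "Then participants wear the accelerometers for 7 consecutive days". The time frame is short: "point data collection is conducted within two weeks at each assessment". The wear week is meant to show usual behaviour: "Participants are instructed to continue with their normal daily routines during the sessions".

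2.6 Statistical Analyses uses linear regression for the relation of activity and cognitive development over time. Five accelerometer measures are the independent variables and three IQ scores the dependent variables. Covariates or moderators come from the questionnaires and from the anthropometric and fitness assessments. On the mechanism it says: "Exploratory analyses are also performed in order to examine whether plasma IGF-1 and BDNF concentrations serve as the mediators". Neither analysis names the wave from which exposure, mediator and outcome are taken, and earlier IQ does not appear in the covariate list.

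The Abstract says these regressions examine the effect of physical activity on cognitive development. 2.2 makes blood sampling optional at every wave. 3 Results reports that in the pilot of 36 children "venous blood samples were taken from 66.7% of children".

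**The concern.** The study's aims are directional: whether activity contributes to cognitive development, and whether it does so through IGF-1 or BDNF. The Discussion justifies the study by the shortage of longitudinal evidence. Repeated waves help with direction only if the model puts the exposure before the outcome and holds earlier IQ fixed. The model in 2.6 would be satisfied equally well by regressing IQ on activity from the same wave.

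In that case a child whose cognitive level shapes how active he or she is produces the same coefficient as a child whose activity shapes cognition. The mediation has the same ambiguity, because concurrent levels of activity, growth factor and IQ do not show which came first. Five activity measures and three IQ scores are to be analysed at up to six waves, so many associations could be described as effects.

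There is a second, smaller issue. Because blood is optional, a total effect estimated in all children and an indirect effect estimated in blood donors would refer to different groups unless one analysis sample is fixed.

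**Working it through.** **Inputs from the article.** Six waves three years apart; 500 children; blood from 66.7% of 36 pilot children, that is 24. The article gives no effect size, alpha or correlation between waves. The path values below, the two-sided 0.05 level and the correlations between waves are assumptions.

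**Step 1. The plan's own figure.** Span = (6 − 1) × 3 = 15 years, as stated.

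**Step 2. What the waves can supply.** Activity at wave k with IQ at wave k+1: 6 − 1 = 5 pairs. Activity at k, growth factor at k+1, IQ at k+2: 6 − 2 = 4 sequences. The planned data can therefore provide the time order.

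**Step 3. Same-wave regression under reverse causation only.** Let activity have no effect on IQ, and let IQ affect activity with standardised path r. The same-wave correlation is then r, and the chance of a significant result is about Φ(r√n − 1.96), with √500 = 22.36.

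| r (assumed) | r√500 | Significant |
|---|---|---|
| 0.05 | 1.12 | 20% |
| 0.10 | 2.24 | 61% |
| 0.15 | 3.35 | 92% |
| 0.20 | 4.47 | 99% |

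In the lagged model the partial correlation of activity at wave k with IQ at wave k+1, given IQ at wave k, is zero under this scenario, so the rate should be 5%. Simulation (2,000 data sets per setting, IQ autocorrelation 0.7) gave 4% to 6%.

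**Step 4. Same-wave mediation.** Assume standardised paths of 0.3 and reliability 0.7 for the 7-day record as a measure of habitual activity.
- Forward chain, activity → mediator → IQ: the activity–mediator coefficient is 0.3 × √0.7 = 0.251, the mediator–IQ coefficient given activity is 0.3, and the product is 0.075.
- Reversed chain, IQ → mediator → activity: the recorded activity–mediator correlation is again 0.3 × √0.7 = 0.251, the mediator–IQ coefficient given activity is again 0.3, and the product is again 0.075.

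The two chains imply the same correlations, so no same-wave test can separate them. In simulation the indirect effect was significant in over 99% of runs in both directions, at n = 333 and n = 500.

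**Step 5. Does the lag also deal with stable traits?** Assume no causal path either way, and one stable trait loading λ on both IQ and activity. Assume also an autocorrelation of 0.5 in the rest of IQ. The same-wave correlation is s = λ², the IQ correlation between waves is q = s + 0.5(1 − s), and the lagged partial correlation is s(1 − q)/√[(1 − q²)(1 − s²)].

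| λ (assumed) | s | q | Lagged partial | Lagged significant | Same-wave significant |
|---|---|---|---|---|---|
| 0.3 | 0.09 | 0.545 | 0.049 | 19% | 52% |
| 0.4 | 0.16 | 0.580 | 0.084 | 46% | 95% |
| 0.5 | 0.25 | 0.625 | 0.124 | 79% | 100% |

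The lag reduces this error but does not remove it.

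**Step 6. Blood subset.** If the pilot rate carries over, 500 × 24/36 = 333 children have blood at a given wave.

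**The case against.** The strongest reply is that 2.6 nowhere says the analysis is same-wave. It speaks of a relation over time, the design is longitudinal, and a condensed article commonly leaves lag structure to a fuller plan. Much of this stands: a reader might infer that the study ignores its six waves, and the text does not support that. The article does, however, go as far as naming model type, exposures, outcomes and covariate sources. That list, read with the Abstract's description of an effect, leaves the uninformative model permitted.

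A reader might also infer from the order in 2.4 that the cause is measured after its effect, which alone would invalidate the estimate. The documents do not support this either. The gap is a week or two, and the wear week follows normal routines, so it stands in for habitual activity. In Step 4 the forward pathway was still detected with the later record. Moving the device ahead of the IQ test would change nothing of substance; the limitation is concurrency.

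Third, the mediation is already labelled exploratory, and the aim is worded as exploring whether a pathway exists. That stands, and it lowers the stakes for the mediation but not for the main regression. Family, education, occupation and income data are collected as potential covariates, which covers part of the stable confounding.

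Fourth, Step 3 builds in reverse causation, so the lagged model's 5% follows by construction. This is fair, and Step 5 is the counterweight. Finally, one could compute 500 × (24/36)⁶ = 44 children with blood at all six waves. That assumes independent opt-in at each wave, whereas willingness to give blood probably persists, and three-wave mediation does not need all six samples. The figure should not be relied on.

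**Conclusion.** The point holds as a weakness in the stated model, not as an error in the order of data collection. As written, 2.6 allows a same-wave regression and mediation, and these cannot distinguish activity affecting cognition from the reverse. Under pure reverse causation with assumed paths of 0.05 to 0.20, the same-wave regression would mislead in about 20% to 99% of studies of 500 children, against about 5% for the lagged model adjusted for earlier IQ. Under a shared stable trait with assumed loadings of 0.3 to 0.5, the lagged model is still falsely significant in 19% to 79%, compared with 52% to 100% same-wave.

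These rates illustrate size and are not forecasts. They assume the stated paths, complete data on 500 children, and IQ measured without error; error in the earlier IQ score would let some reverse causation through. The algebraic result in Step 4, that both mediation directions imply the same correlations, needs no particular path size. A fuller plan that already states the lag would settle the point.

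**What to change.** In 2.6, state the pairing. The main model is activity at wave k predicting IQ at wave k+1, adjusted for IQ at wave k and the planned family and socioeconomic covariates. For the exploratory mediation, take activity, growth factor and IQ from successive waves. Estimate total and indirect effects on one defined sample. Report same-wave results as associations only, and align the Abstract's wording with this. Add a random-intercept (within-person) model as a sensitivity analysis for stable traits.

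No new measurement is needed, and first-wave collection was still under way when the article was written, so the model can be fixed before follow-up data exist. The costs are real. The first effect estimate waits for wave 2 and mediation for wave 3. Wave 1 IQ serves only as baseline, and activity at wave 6 has no later outcome. The lag is three years, so shorter-acting effects may be missed. Without the random-intercept analysis, stable family traits remain only partly controlled.
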